#### Secondary endpoint objectives

2.2.2

An overview of the secondary objectives is given in Table 3. The secondary objectives are patient related outcome measures (PROMs), major adverse cardiac events (MACE) and safety endpoints. MACE consists of the following components; (i) number of hospital admissions due to an acute coronary syndrome (ACS), (ii) undergoing revascularization (PCI and/or CABG), (iii) number of presentations at the emergency room due to angina pectoris and, (iv) cardiovascular mortality. ACS is defined in accordance with the universal definition of myocardial infarction as a high‐sensitivity troponin T with at least one value above the 99th percentile of the upper reference limit with at least one of the following; (1) symptoms of myocardial ischemia, (2) new ischemic electrocardiographic changes, (3) development of pathological Q waves, (4) imaging evidence of loss of viable myocardium or new regional wall motion abnormality or, (5) intracoronary thrombus detected on angiography or autopsy.^17^ The clinical endpoints will be investigator reported. The Seattle Angina questionnaire (SAQ; Appendix 3), RAND 36‐item Health Survey (RAND‐36; Appendix 4) questionnaire, Numeric Rating Scale (NRS‐scale; Appendix 5), CCS class, 6‐min walking test (6‐MWT), and review of patient files will be used to obtain the secondary objectives (Table 3).

**Table 3 clc24016-tbl-0003:** Secondary objectives.

Changes in absolute quantification of myocardial blood flow using myocardial perfusion PET scan including myocardial blood flow & myocardial flow reserve regionally and globally.
Patient related outcome measures: ○ Patient condition using 6‐minute walking test; ○ Frequency of angina pectoris using the SAQ; ○ Severity of angina pectoris using the Numeric Rating Scale; ○ Grading of angina pectoris using the Canadian Cardiovascular Society class; ○ Quality of life using the RAND 36‐item Health Survey; ○ Frequency of short‐acting nitrate use using the SAQ.
Major Adverse Cardiac Events: ○ Number of hospital admissions due to acute coronary syndrome; ○ Revascularization (CABG and/or PCI); ○ Number of presentations at the emergency room due to angina pectoris; ○ Cardiovascular mortality.
Safety endpoints; ○ Number of device infections (lead and/or battery); ○ Number of device dislocations (lead and/or battery); ○ Number of lead fractures/breakages; ○ Number of lead failures; ○ Number of battery end of life.

Abbreviations: CABG, coronary artery bypass grafting; PCI, percutaneous coronary intervention; PET, positron emission tomography; SAQ, Seattle angina questionnaire.

### Follow‐up

2.3

At baseline the SAQ, RAND‐36, NRS‐scale, and CCS class will be completed when the patient is seen for the initial standardized TENS treadmill test. The baseline 6‐MWT will be performed after the baseline myocardial perfusion PET scan has shown myocardial ischemia. After spinal cord stimulator implantation the follow‐up appointments will take place at the outpatient clinic of the department of anesthesiology. Patients will be seen at the outpatient clinic one week (to check the surgical wounds), 1, 3, 6 months, and 1 year after initial spinal cord stimulator implantation.

At 6 months the myocardial perfusion PET scan will be repeated before the 6‐month outpatient clinic appointment. The SAQ, RAND‐36, NRS‐scale, CCS class, and 6‐MWT will be completed when the patient is seen for the 6‐month outpatient clinic visit. After confirmation that all data are complete by a member of the research team (excluding the study nurse), the patient has an appointment with the study nurse. At this appointment the study nurse will change the programming according to the randomization, from “SCS ON” to “SCS OFF” or vice versa. The programming of the spinal cord stimulator is performed in the same manner and by the same study nurse as was done at baseline ensuring that the blinding of the patient and the rest of the research team remains intact. At 12 months the myocardial perfusion PET scan will be repeated before the final, 12‐month outpatient clinic appointment. Additionally the SAQ, RAND‐36, NRS‐scale, CCS class, and 6‐MWT will be completed when the patient is seen for the final outpatient clinic appointment by a member of the research team in the same fashion as the 6 month appointment. At this final appointment, after confirmation of complete data, the spinal cord stimulator settings will be set to conventional spinal cord stimulation by the study nurse in the same manner as the 6 month appointment. In addition the patient will be asked during which period of the study, the first or second 6 months, it was thought that the spinal cord stimulator was turned on.

For the duration of the study patients are asked to contact our center to inform us if visits to the emergency room, admissions to hospital and/or the undergoing of a PCI and/or CABG have occurred. If complications arise related to the implanted spinal cord stimulator (i.e., signs of infection, battery dislocation, lead dislocation, and/or lead fracture) patients will be asked to contact the outpatient clinic of the department of anesthesiology to determine the appropriate course of action.

After completion of the study patients will be invited to the outpatient clinic each year for a total duration of 5 years for long‐term follow‐up. At each outpatient clinic appointment patients will be asked to complete the SAQ, RAND‐36, NRS‐scale, CCS class, and 6‐MWT.

### Sample size calculation

2.4

Currently, no data with regard to the percentage of myocardial ischemia (as % of the left ventricular myocardium) present in patients with RAP using myocardial perfusion PET scan as imaging modality are available. The data available on this subject is with the imaging modality MIBI‐SPECT. The percentage of myocardial ischemia (as % of the left ventricular myocardium) present in patients with refractory angina pectoris using MIBI‐SPECT ranges from 6.12% (standard deviation of 3.7)^18^ up to 14.01%.^19^ Combining this data, it translates into an average percentage of myocardial ischemia of 10% with a standard deviation of 7.

Using these clinical assumptions (average percentage of myocardial ischemia of 10% and a standard deviation of 7) and the typical assumptions (paired, two‐tailed *T* test, *α* .05 and power .80) a sample size of 32 patients per arm (total 64 patients) could detect a relative reduction in percentage of myocardial ischemia of 25%. Assuming a 10% patient drop‐out in the analysis, this means a total of 72 patients should be included in the study.

Due to the study design using cross‐over, it is theoretically possible that a carry‐over and/or period effect could occur. We will apply the two‐stage approach as proposed by Grizzle et al to assess the carry‐over and period effect.^20^ To assess the carry‐over effect we will first determine the summed effect over the two periods and compare these between the two groups (A and B). In the same way we will assess the period effect by determining the summed effect over the two groups and compare these between the periods. When analyses show that the carry‐over effect as well as the period effect are negligible, we will use a paired, two‐tailed Students’ *T* test for the main outcome parameter. If a significant carry‐over effect is found, only data from the first period will be analyzed. Due to the long study period of 6 months before performing the PET scan after cross‐over has taken place, the assumption is that there will not be a carry‐over effect.

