## LIMITATIONS

5

There are a number of limitations with regard to the SCRAP trial. One limitation is the difference in myocardial ischemia on which the sample size calculation is based. The power of the study is based on a relative reduction in myocardial ischemia of 25% after treatment with SCS, in absolute numbers a reduction from 10% to 7.5% of myocardial ischemia. Whilst this is a relatively modest difference, it is deemed clinically relevant. Patients with more than 10% myocardial ischemia have a worse prognosis in comparison to patients with less than 10% myocardial ischemia,^15^ making the chosen difference clinically relevant. A second limitation of the study is the single‐center design and the reason for this choice is twofold. Firstly the number of patients meeting the selection criteria is expected to be low. Second, the implantation of spinal cord stimulators should be limited to specialized centers to reduce the risk of device‐related complications and the chosen center for the SCRAP trial is such a specialized center.^26^, ^27^

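### The only named primary test requires a negligible period effect, and no analysis is stated for a period effect without carry-over

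*Protocol article*

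**What the plan says.** Section 2.4 (Sample size calculation) of the protocol article accepts that carry-over or period effects are theoretically possible and adopts a two-stage approach. Carry-over is assessed by comparing sums over the two periods between groups A and B. The period effect is assessed by comparing sums over the two groups between the periods. The rule for the main outcome then has two branches:

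- If analyses show that the carry-over "effect as well as the period effect are negligible, we will use a paired" two-tailed t-test.
- If carry-over is significant, only first-period data are analyzed.

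No other primary test is named. The same section argues that carry-over is not expected, because 6 months pass between the switch and the second scan. It gives no matching argument about the period effect.

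The sample size rests on the same test, under "typical assumptions (paired, two‐tailed *T* test" with two-sided 5% and 80% power. The inputs are an "average percentage of myocardial ischemia of 10% and a standard deviation of 7", and the result is that "a sample size of 32 patients per arm (total 64 patients) could detect" a 25% relative reduction. Section 5 (Limitations) gives this as "in absolute numbers a reduction from 10% to 7.5% of myocardial ischemia". After 10% drop-out, "this means a total of 72 patients should be included in the study".

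**The concern.** The first branch needs two conditions, but the second covers the failure of only one. If the period comparison is not negligible and carry-over is not significant, the article leaves the trial without a primary analysis. Because negligible is undefined, whether that situation has arisen is itself a judgement made on outcome data.

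A period effect needs no such gate. In a two-period cross-over it is a nuisance term that can simply be in the model. Leaving it out has two possible consequences. With equal sequences, the test uses too large a standard error and loses power. With unequal numbers of completers, part of the period effect enters the treatment estimate.

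A period effect is plausible here. Section 1 (Introduction) describes an earlier stimulation study in which ischemia was lower at 12 months but not at 3, and whose authors suggested improved collateralization through physical activity as the reason. Slow change of that kind could make the 12-month scans differ from the 6-month scans whatever the device setting.

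**Working it through.** **Inputs.** From the article: effect 2.5 points (10% to 7.5%), SD 7, two-sided 5%, 64 analyzed, 72 enrolled. Assumed: 7 is the SD of within-patient differences, which the article does not say, and the period effect p (second period minus first) is 2 to 5 points, because the article gives none. The paired difference is taken as stimulation ON minus OFF.

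**1. The plan's own figure.** For a paired t-test the noncentrality is (2.5/7) × √64 = 2.86, and power is 0.803. The smallest n with power of at least 0.80 is 64 (the normal approximation gives 62). 64/0.9 = 71.1, rounded up to 72. Both figures reproduce. If 7 is instead the between-patient SD, this corresponds to a within-patient correlation of 0.5.

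**2. How p enters.** Let τ be the treatment effect. The expected ON − OFF difference is τ − p for patients who have ON first and τ + p for those who have OFF first. With n1 and n2 completers, the mean difference estimates τ − p(n1 − n2)/(n1 + n2). The bias is zero when n1 = n2.

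**3. Balanced sequences (32/32).** The true standard error of the mean difference is 7/√64 = 0.875 for any p. The unadjusted test estimates its SD as about √(49 + p²); at p = 3 that is 7.62, a standard error of 0.95. The test is therefore conservative. Simulation (100,000 to 200,000 trials per case):

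| p (points) | Power, unadjusted | Type I error, unadjusted | Power, adjusted |
|---|---|---|---|
| 0 | 0.80 | 0.050 | 0.80 |
| 2 | 0.78 | 0.042 | 0.80 |
| 3 | 0.75 | 0.032 | 0.80 |
| 4 | 0.71 | 0.025 | 0.80 |
| 5 | 0.66 | 0.016 | 0.80 |

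**4. Unequal completers.**

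- 36/28, p = 3: bias 3 × 8/64 = 0.38 points in size, which is 15% of 2.5. Type I error is about 0.05.
- 38/26, p = 3: bias 3 × 12/64 = 0.56 points. Type I error is about 0.07, and about 0.09 at p = 5.

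**5. Period-adjusted test.** Averaging the two sequence means of ON − OFF gives a standard error of (7/2) × √(1/n1 + 1/n2): 0.875 at 32/32, 0.882 at 36/28 and 0.891 at 38/26. Simulated type I error is about 0.05 and power 0.79 to 0.80 in every case.

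**6. The period test as a gate.** If negligible means not significant at 5%, then with 32/32 the period test would flag p = 1.25, 2, 3 and 4 in about 29%, 61%, 92% and 99% of trials.

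**7. The carry-over fallback.** First-period data only, 32 per group, SD 7: power about 0.29.

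**The case against.** The case on the other side limits the size of the point more than its substance.

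- **The gate would usually stop the paired test where it does most harm.** This stands. At 3 or 4 points a 5% period test flags the effect in 92% to 99% of trials, so the paired test would seldom be run. What remains in those cases is the missing branch. For smaller effects the gate is weak, but the loss is small too (0.80 to 0.78 at 2 points).
- **The imbalance examples are extreme.** This stands. Starting from 36/36, a 36/28 split needs all eight drop-outs in one sequence; with drop-out unrelated to sequence, that has probability 2 × C(36,8)/C(72,8) ≈ 0.005. A 38/26 split among 64 completers also needs unequal randomization, since one sequence must start with more than 36.
- **The full protocol or analysis plan may hold the missing branch, and the cited two-stage method may imply an adjusted test.** Possible, but the article cites the method for assessing the two effects, then itself names the unadjusted paired test and sets a rule with a branch absent.

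Three stronger readings are tempting. A reader might infer that a period effect is likely, since implantation opens the first period and visits cluster there ("Patients will be seen at the outpatient clinic one week (to check the surgical wounds), 1, 3, 6 months, and 1 year after" implantation). The article links neither surgery nor visit frequency to PET ischemia, so plausible is as far as the text goes. A reader might also infer that the method is chosen on unblinded results. The period comparison pools the two groups, so it does not require knowing which group had stimulation first; the method depends on outcome data, and no more can be said. Finally, a reader might treat p as random error, with SD √(49 + p²), and obtain power of 0.73 and 0.69 at 3 and 4 points. That overstates the loss: with fixed equal sequences p cancels from the mean, and the simulated values are 0.75 and 0.71.

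**Conclusion.** The point holds. Section 2.4 makes its only named primary test conditional on an undefined absence of a period effect, and it gives no analysis for a period effect without carry-over. That follows from the text and needs no numerical assumption.

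The numerical cost is moderate and rests on assumed period effects and on 7 being the SD of within-patient differences. With balanced sequences the unadjusted test is valid, unbiased and conservative, and gives up about 2 to 9 percentage points of power for period effects of 2 to 4 points. Bias and inflated type I error need unequal sequences, and the inflation appears only at splits more extreme than 36/28. This should be corrected before the primary analysis, but it does not undermine the design or the sample size.

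**What to change.** In section 2.4, replace the conditional paired t-test and the period pre-test with one prespecified primary analysis: a linear mixed model of percentage ischemia at 6 and 12 months, with fixed effects for treatment (ON/OFF) and period and a random patient effect, reported as the treatment effect with a 95% confidence interval. With complete data this equals a two-sample t-test comparing within-patient period differences between sequences. The model can also keep patients with only one scan after implantation, under a missing-at-random assumption.

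State that this analysis is primary whatever the period or carry-over assessment shows, and make any first-period analysis a sensitivity analysis. Removing the period pre-test alone would leave the primary method conditional on the carry-over test, with a fallback of about 0.29 power.

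Section 2.2.1 words the primary objective as change from baseline under stimulation, so say there that the tested contrast is ON versus OFF. A common baseline cancels from that within-patient contrast.

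The cost is a change of wording and one degree of freedom. The sample size stays at 64, or 72 with drop-out.

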Although the exact working mechanism of SCS in RAP has not been elucidated studies have repeatedly shown an improvement in the quality of life and a reduction in angina symptoms.^7^, ^8^, ^9^, ^11^, ^12^, ^13^ It is unclear if SCS leads to reduction in the amount of myocardial ischemia. One study by Diedrichs et al. determined the effect of SCS based on the amount of myocardial ischemia using Methoxyisobutylisonitrile single photon emission computed tomography (MIBI‐SPECT).^14^ All patients were treated with SCS and MIBI‐SPECT was performed at baseline, 3 and 12 months. After 12 months, there was a significant reduction in the amount of myocardial ischemia that was not seen at 3 months. Because the reduction of myocardial ischemia was only seen at 12 months, the authors concluded that this effect might not have been a direct effect of SCS, but rather due to better coronary collateralization created by enhanced physical activity. Thus, the question remains whether SCS actually reduces the amount of myocardial ischemia.

The recently published European Society of Cardiology (ESC) guideline “Chronic Coronary Syndromes” describes varying levels of evidence with regard to treatment options in patients with RAP. The ESC guideline concludes that SCS may be considered (Class of recommendation IIB; level of evidence B).^15^ It summarizes that “Larger RCTs are required to define the role of each treatment modality for specific subgroups, to decrease nonresponder rates and ascertain benefit beyond potential placebo effects,” confirming the need for additional studies.^15^

The type of SCS traditionally used in patients with RAP is conventional stimulation. With this type of stimulation the patient will feel paresthesia at the target area. For this study a paresthesia free form of stimulation, high density (HD) stimulation, will be applied. Based on previous experience it is a viable treatment modality, it allows adequate blinding of patients because no paresthesia are felt and the patient can be fully informed about the fact that the spinal cord stimulator will be turned off for a period of 6 months.^16^ This is in contrast to previous studies in which blinding of patients has been problematic due to the paresthesia felt by the patient.^6^, ^7^, ^8^, ^9^

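### The carry-over pre-test with first-period fallback makes the primary test exceed its 5% level: about 7.3–8.2% at the correlation that the sample size implies

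*Protocol article*

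**What the plan says.** Section 2.4 (Sample size calculation) adopts the Grizzle two-stage approach. Each patient's two period values are summed and the sums are compared between sequences A and B to assess carry-over; a similar comparison between periods assesses the period effect. If both are judged negligible, the main outcome is tested with a paired two-tailed t test. If a significant carry-over "effect is found, only data from the first period will be analyzed". The article gives no level for the carry-over test and no adjustment of the primary alpha for the choice between analyses.

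The same section expects no carry-over because of the six months that pass before the scan: once cross-over "has taken place, the assumption is that there will not be a carry"-over effect. The sample size is derived for the paired test only, from an "average percentage of myocardial ischemia of 10% and a standard deviation of 7", giving "a sample size of 32 patients per arm (total 64 patients") before drop-out. Section 5 (Limitations) states the target effect as "in absolute numbers a reduction from 10% to 7.5% of myocardial ischemia".

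**The concern.** The choice of primary test depends on the data that the test then uses. The carry-over contrast is built from period 1 plus period 2, and the fallback compares period 1 alone. If the sequences differ by chance in period 1, the pre-test is more likely to be significant and the period-1 comparison is likely to be significant too. The fallback is therefore used selectively in the trials where it is most likely to reject, and the single primary p-value no longer has its stated 5% level.

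The gate is also weak as a safeguard. The comparison of sums is between patients and carries the full between-patient variation, so a non-significant result says little about whether carry-over is negligible. Carry-over cannot be ruled out from the article's own background. The Introduction describes a MIBI-SPECT study with less ischemia at 12 months but not at 3, which its authors thought might not be a direct effect of stimulation but "rather due to better coronary collateralization created by enhanced physical activity". That such a change could outlast switch-off is an inference; the article does not say so.

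**Working it through.** **Inputs.** Section 2.4: two-sided alpha 0.05, power 0.80, SD 7, 32 per sequence, 10% drop-out. Section 5: effect 10 − 7.5 = 2.5 points. Assumed, because not stated: within-patient correlation ρ from 0 to 0.8 and pre-test level 0.05 or 0.10.

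**1. The plan's own figure.** A paired t test with SD of differences 7 and effect 2.5 needs n = 64 (exact power 0.803), and 64/0.9 = 71.1, rounded up to 72. Both match the article. If 7 is also the SD of a single scan, then 7 = 7√(2(1 − ρ)), so ρ = 0.5. This is the correlation implied by the sample size.

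**2. Type I error.** The correlation between the carry-over contrast and the period-1 contrast is √((1 + ρ)/2), which is √0.75 = 0.866 at ρ = 0.5. Under normality with equal variances, sums and differences are independent, so

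overall error = a × P(period-1 test rejects | fallback) + (1 − a) × 0.05,

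where a is the pre-test level. From the bivariate normal distribution with correlation 0.866, the conditional probability is about 0.53 for a = 0.05 and 0.37 for a = 0.10:

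- a = 0.05: 0.05 × 0.53 + 0.95 × 0.05 = 0.074
- a = 0.10: 0.10 × 0.37 + 0.90 × 0.05 = 0.082

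Simulation of the carry-over gate with t tests (32 per sequence, SD 7, no effects) agrees:

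| ρ | pre-test 0.05 | pre-test 0.10 |
|---|---|---|
| 0 | 6.5% | 7.1% |
| 0.3 | 7.0% | 7.6% |
| 0.5 | 7.3% | 8.2% |
| 0.7 | 7.9% | 8.6% |
| 0.8 | 8.3% | 9.1% |

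The paired test alone holds 5.0%. At ρ = 0.5, once the fallback is triggered, the period-1 test rejects a true null about 36–54% of the time across simulation runs and the two pre-test levels. With both stages on change from baseline, the overall error is still 7.2–8.2%.

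**3. Power of the gate (ρ = 0.5).** The SD of a patient's sum is 7√(2 × 1.5) = 12.12, and the standard error of the sequence difference is 12.12 × √(2/32) = 3.03. Complete carry-over shifts that difference by 2.5, a ratio of 2.5/3.03 = 0.82. Power is about 13% at level 0.05 and 21% at 0.10. For a 1.25-point carry-over it is about 7% and 13%.

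**4. Unconditional power of the fallback.** The standard error is 7 × √(2/32) = 1.75, and 2.5/1.75 = 1.43. Power is 29% by t test; 80% would need about 125 per arm.

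**5. Effect of carry-over on the two-period estimate.** With carry-over λ from ON into a following OFF period, the ON–OFF difference is 2.5 − λ in one sequence and 2.5 in the other, averaging 2.5 − λ/2. Complete carry-over (λ = 2.5) gives 1.25; λ = 1.25 gives 1.875.

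**The case against.** The rule is prespecified, and without carry-over the fallback would be triggered in only 5–10% of trials. The excess error at ρ = 0.5 is therefore 2–3 percentage points, and power without carry-over falls only from 0.80 to about 0.79 or 0.77. The correlation and the pre-test level are assumptions, and an analysis plan not shown may fix the level. All this stands and limits the size of the point. It does not remove it: the article itself states the faulty rule, and the error exceeded 5% in every setting tried.

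Three stronger readings are tempting and not supported.

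- **A triggered fallback has almost no chance of finding the target effect.** The 29% is unconditional. At ρ = 0.5 with a 2.5-point effect, the triggered test rejects about 50–52% of the time without carry-over and about 80–90% with carry-over of 1.25 or 2.5 points. The problem is selection bias. Nor is 29% fixed by the article: it takes 7 as the single-scan SD and uses raw values. It becomes 22–60% on change from baseline, or 14–38% if 7 is strictly the SD of differences (ρ from 0.3 to 0.8 in both).
- **Undetected carry-over halves the estimate because of this rule.** Halving needs complete carry-over, and the same bias affects an unconditional paired analysis. Under complete carry-over the paired test alone has about 28% power, against 36–39% for the two-stage rule. The case for change is type I error.
- **The background shows that carry-over will occur.** The cited authors were tentative, and section 4 (Discussion) cites blood-flow changes after 3–6 weeks of stimulation, which suggests a faster onset. Neither speaks to how the effect wears off.

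**Conclusion.** The point holds as a fault in the stated primary analysis. The two-stage rule does not keep its two-sided 5% level. The error is about 7.3–8.2% at correlation 0.5, which rests on 7 being both the single-scan SD and the SD of differences. It is about 6–9% over correlations 0–0.8 and pre-test levels 0.05–0.10. The calculations assume normal data, equal variances and 32 evaluable patients per sequence, and they model the carry-over gate only, not the period-effect gate.

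The rule gives little protection in return, since a non-significant pre-test does not show that carry-over is negligible. The sample size supports only the paired test, and a first-period result reached through the gate is biased by selection.

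**What to change.** - Delete the two-stage gate, for both the carry-over and the period effect.
- Make a within-patient ON versus OFF analysis of both periods, adjusted for period, the unconditional primary analysis.
- Reconcile this with section 2.2.1 (Primary endpoint objective), which describes the end of the SCS period compared with baseline rather than with the OFF period.
- Report the carry-over contrast as an estimate with a confidence interval, not as a decision rule.
- Always report, as supportive, a period-1 ON versus OFF ANCOVA on the baseline PET already collected. With single-scan SD 7 its power is about 37% at correlation 0.5 and 50% at 0.7, so it is no substitute for the primary analysis.
- State that the primary analysis assumes no carry-over, and that carry-over of benefit would bias the estimate towards zero (halving it only if complete).

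The cost is a change to the analysis text and the endpoint wording, with no new patients, scans or visits. It should be settled before unblinding. The change restores the type I error; the exposure to carry-over bias remains and has to be argued from the design.
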